### Sample size

The sample size was calculated with the aid of the STATA 11 program and based on a study carried out by Grecco *et al.*[35] (*Effect of treadmill training without partial weight support on functionality in children with cerebral palsy: Randomized controlled clinical trial*). The Six-Minute Walk Test was considered for the calculation. This test was selected as the primary outcome based on its proven validity and reliability as a functional capacity assessment tool and will be used to evaluate the functional mobility and physical fitness of children with CP. Considering a mean and standard deviation of 377.2 ± 93.0 m in the experimental group and 268.0 ± 45.0 m in the control group, a bidirectional alpha of 0.05 and an 80% test power, eight children will be required for each group, to which 25% will be added to compensate for possible dropouts, totaling 40 participants (10 in each group).

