### Evaluation and follow-up

The children in both groups will be evaluated by two physical therapists experienced in the evaluation procedures and blinded to which group each child belongs. Four evaluations will be carried out:

Evaluation 1: one week prior to intervention;

Evaluation 2: one week following intervention;

Evaluation 3: one month following the end of intervention;

Evaluation 4: three months following the end of intervention.

Evaluations will be held on two non-consecutive days.

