### Statistical analysis

The Kolmogorov-Smirnov test will be used to determine whether the data adhere to the Gaussian curve. Parametric data will be expressed as mean (standard deviation) and nonparametric data will be expressed as median (inter-quartile interval). The effect size will be calculated by the difference between means of the pre-intervention and post-intervention evaluations and will be presented with the respective 95% confidence interval. Either repeated-measures ANOVA or Friedman’s test will be used for the statistical analysis of the immediate effects of tDCS for parametric and nonparametric variables, respectively. Either two-way ANOVA or the Kruskal-Wallis test will be used for the statistical analysis of the effects of mobility training with and without tDCS for parametric and nonparametric variables, respectively. All p-values < 0.05 will be considered significant. The data will be organized and tabulated using the Statistical Package for the Social Sciences (SPSS v.19.0).

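### Repeated-measures ANOVA or Friedman's test is tied to an immediate tDCS effect that the schedule cannot measure, and the evaluations it uses are not stated

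*Protocol article*

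**What the plan says.** The Statistical analysis section of the protocol article names two families of tests. For the first, either repeated-measures ANOVA or Friedman's "test will be used for the statistical analysis of the immediate effects of tDCS". The second, two-way ANOVA or Kruskal-Wallis, is for training with and without tDCS; no time factor is named. The effect size is a difference between pre- and post-intervention means. Software appears in one sentence: "The data will be organized and tabulated using the Statistical Package for the Social Sciences (SPSS v.19.0").

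Evaluation and follow-up states: "Four evaluations will be carried out". One precedes the intervention and three follow it, at one week, one month and three months. The earliest is "Evaluation 2: one week following intervention". The Intervention section places tDCS within the training sessions, and the training protocols run for two weeks.

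Sample size gives "a bidirectional alpha of 0.05 and an 80% test power, eight children will be required for each group". An allowance for losses then raises that number by a quarter, to ten per group and 40 children in all.

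Hypothesis 1 concerns training with tDCS against the same training without it, so the contrast of interest lies between groups.

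**The concern.** Three things do not fit together.

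- **The label and the schedule.** No outcome is scheduled during a tDCS session, straight after it or on the same day. A result from Evaluation 2 would be reported as immediate although it is measured a week after stimulation ends.
- **The unnamed evaluations.** Classical repeated-measures ANOVA and Friedman's test both use only children with every measurement that is entered. Whether this matters depends on which evaluations are entered, and the section does not say.
- **The nonparametric branch.** Friedman's test compares repeated measurements within one set of subjects. It has no between-group factor, so it cannot test active against placebo tDCS.

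At stake are the number of children behind the one-week comparison, possible bias if loss to follow-up is related to response or tolerance, and whether the later evaluations have a defined analysis.

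**Working it through.** **1. The plan's own sample size.** Inputs from Sample size: "377.2 ± 93.0 m in the experimental group and 268.0 ± 45.0 m in the control group", two-sided alpha 0.05, power 80%.

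- Difference: 377.2 − 268.0 = 109.2 m.
- Root-mean-square SD: √((93.0² + 45.0²)/2) = 73.05 m.
- n per group = 2 × (73.05 × (1.960 + 0.842)/109.2)² = 7.03, rounded up to 8. This reproduces the stated figure.
- 8 × 1.25 = 10 per group, 40 in total. This also reproduces. Because 8/(1 − 0.20) = 10, adding 25% covers a 20% loss.
- Power with 8 per group is 85% by normal approximation and 79% by noncentral t.

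**2. Reading A: all four evaluations enter.** The documents give no rate of missed visits. Assume baseline is complete and each of the three follow-up evaluations is missed independently with probability m. The complete fraction is (1 − m)³. Power is for two groups of the resulting size on the inputs above, Φ(109.2/(73.05 × √(2/n)) − 1.960). The last column gives the children kept if only Evaluations 1 and 2 enter.

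| m | (1 − m)³ | Complete per 10 | Complete of 40 | Power | Of 40, Evaluations 1 and 2 only |
|---|---|---|---|---|---|
| 2% | 0.941 | 9.4 | 37.6 | 90% | 39.2 |
| 5% | 0.857 | 8.6 | 34.3 | 87% | 38.0 |
| 7.2% | 0.800 | 8.0 | 32.0 | 85% | 37.1 |
| 10% | 0.729 | 7.3 | 29.2 | 81% | 36.0 |
| 15% | 0.614 | 6.1 | 24.6 | 75% | 34.0 |
| 20% | 0.512 | 5.1 | 20.5 | 67% | 32.0 |

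The planned allowance is used up at m = 1 − 0.80^(1/3) = 0.0717, about 7.2% per visit.

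Dropout may instead be monotone. If 5% are lost by Evaluation 2 and 20% by Evaluation 4 (assumed), the one-week comparison uses 8 rather than 9.5 children per arm. Its variance is then 9.5/8 = 1.19 times as large, although the week-one values were collected.

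**3. Reading B: only Evaluations 1 and 2 enter.** A later missed visit then removes nobody. What remains for one month and three months is the two-way ANOVA or Kruskal-Wallis test, which has no stated time factor or evaluation, and a pre/post effect size. No longitudinal analysis is clearly assigned to these two evaluations.

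**4. Both readings.** The first post-treatment value is taken one week after the course, so neither reading yields an immediate effect. Under neither does Friedman's test contain the active-versus-placebo contrast.

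**The case against.** A reader might infer that the plan drops every child who misses any of the four evaluations, that SPSS causes this, and that the dropout allowance contradicts it. The documents do not support that.

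- The section does not say that all four evaluations enter. An analysis of immediate effects would most naturally compare Evaluation 1 with Evaluation 2, and a child lost at three months would then keep the one-week value.
- SPSS is named only for organizing and tabulating, and it can also fit mixed models. Any complete-case restriction comes from the named tests.
- Raising 8 to 10 per group is consistent with a complete-case analysis up to 20% loss. The monotone scenario leaves exactly the planned 8. Falling below 8 needs assumed miss rates above about 7.2% per visit under Reading A.
- A tDCS comparison pooled over both training modes has about 12 children per side (2 × 6.1) even at a 15% miss rate.

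It would also be too strong to say that the later evaluations have no analysis at all. The two-way ANOVA is not restricted to any evaluation, and Kruskal-Wallis does compare groups. Finally, a missing-data rule is commonly left to the full protocol or SAP, so its absence from an article is no finding.

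All of this stands and limits the point. It does not remove it: the article chooses these tests and this label itself, the label does not match the schedule, and each reading leaves a gap.

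**Conclusion.** The point holds in a conditional form. It is certain that the named analysis is attached to an immediate effect while the first measurement comes one week after treatment, and that Friedman's test cannot make the between-group comparison of Hypothesis 1. The rest depends on what the section leaves open. With all four evaluations, about 73% of children would be complete at an assumed 10% miss rate (range 94% to 51% for 2% to 20%). With two evaluations, the one-month and three-month data lack a clearly assigned longitudinal analysis.

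The loss of power is moderate: at 10% missed it is still about 81% by normal approximation on the plan's inputs. The stronger reasons to change are that values already collected could be discarded, that selective loss could bias the comparison, and that the time points need defined contrasts. The miss rates and their independence are assumptions. The analysis should be changed, but this is no fundamental flaw in the trial.

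**What to change.** Replace the repeated-measures ANOVA/Friedman step with a linear mixed model for Evaluations 2 to 4, with children analysed in their allocated arm.

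- **Fixed effects:** tDCS, training mode, tDCS × training, evaluation, and the interactions of these terms with evaluation, adjusted for the baseline value and the GMFCS stratum used in randomisation.
- **Estimation:** REML with Satterthwaite degrees of freedom, and an unstructured covariance across the three evaluations. Name in advance a simpler structure to use if it does not converge.
- **Results:** the tDCS effect at one week, one month and three months. Replace the words about immediate effects with: effect one week after the intervention.
- **Who contributes:** every child with at least one post-treatment value. A child with none contributes no outcome, so report the number of such children by arm. The model is valid if data are missing at random; it does not cure loss that depends on unobserved outcomes.

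If the two-way ANOVA or Kruskal-Wallis test is kept, state which evaluation it uses.

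The cost is analysis wording and slightly more work, with no new data. The model is larger: 3 × 2 × 2 = 12 cell means plus 2 covariate terms, and 6 covariance parameters if unstructured, in about 40 children. That is why the fallback covariance is needed.

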### Randomization

Following written agreement from parents/guardians to the participation of their children, those who meet the eligibility criteria will be randomly allocated to one of the four study groups using a block randomization method:

• Group 1: treadmill training with placebo tDCS;

• Group 2: treadmill training with active tDCS;

• Group 3: mobility training with virtual reality and placebo tDCS;

• Group 4: mobility training with virtual reality and active tDCS.

Randomization will be stratified based on the GMFCS (levels I-II and level III). For each stratum, the allocation sequence will be determined using a randomization table. Following the pre-intervention evaluation, the participants will be allocated to the different groups based on the cards contained within sequentially numbered opaque envelopes. This process will be carried out by a member of the research team who is not involved in the recruitment process or development of the study.

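### The named between-group test has no term for the GMFCS stratum and no baseline covariate, so a 40-child trial gives up precision that an ANCOVA on data already scheduled would recover

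*Protocol article*

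**What the plan says.** The Six-Minute Walk Test is the primary outcome; the Sample size section states: "This test was selected as the primary outcome based on its proven validity and reliability". Allocation is restricted on motor function: "Randomization will be stratified based on the GMFCS (levels I-II and level III". A pre-treatment measurement is scheduled under Evaluation and follow-up: "Evaluation 1: one week prior to intervention".

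The Statistical analysis section makes three relevant statements:
- For the effects of training with and without tDCS: "Either two-way ANOVA or the Kruskal-Wallis test will be used".
- For the immediate effects of tDCS: repeated-measures ANOVA, or Friedman's test.
- The effect size is the difference between the pre- and post-intervention means, with a 95% confidence interval.

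The section mentions neither GMFCS nor any covariate. It states neither the two factors nor the response variable of the two-way ANOVA.

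**The concern.** The design treats GMFCS level as important enough to stratify on, but the named between-group test does not use it. If walking distance differs between levels I-II and level III, that difference stays in the error term. The balance forced by stratification is then not credited, and the standard error of the treatment contrast is larger than the design warrants.

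The baseline walk distance is also not used as a covariate. Children across GMFCS I to III are likely to differ widely in walking distance. With 8 to 10 per group, some chance difference at baseline is to be expected even within strata. The rank-based alternatives, Kruskal-Wallis and Friedman, cannot carry either term.

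At stake is the width of the confidence intervals and the power in a trial of 40 children, or 32 if the dropout allowance is fully used.

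**Working it through.** **1. The plan's own figure.** Inputs from the Sample size section: "377.2 ± 93.0 m in the experimental group", "268.0 ± 45.0 m in the control group", "a bidirectional alpha of 0.05 and an 80% test power".
- Difference: 377.2 − 268.0 = 109.2 m.
- Averaged SD: √((93.0² + 45.0²)/2) = 73.05 m.
- n per group = 2 × (1.960 + 0.842)² × 73.05² / 109.2² = 7.03, rounded up to 8.

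This agrees with the article: "eight children will be required for each group". Adding 25% gives 10 per group and 40 in total. No covariate enters this calculation.

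**2. Variance of the between-group contrast**, relative to an analysis of post-intervention values alone, with r the baseline-to-post correlation:
- post-only: 1
- change score: 2(1 − r)
- ANCOVA on baseline: 1 − r²
- ANCOVA relative to change score: (1 − r²)/(2(1 − r)) = (1 + r)/2

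The article gives no r, so a range is assumed.

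| r | Post-only | Change | ANCOVA | ANCOVA / change |
|---|---|---|---|---|
| 0.5 | 1.00 | 1.00 | 0.75 | 0.75 |
| 0.7 | 1.00 | 0.60 | 0.51 | 0.85 |
| 0.8 | 1.00 | 0.40 | 0.36 | 0.90 |

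**3. Power for the tDCS main effect.** This uses 8 per group, hence 16 v 16, with SD 73.05 m and two-sided alpha 0.05. The assumed effect is 109.2/2 = 54.6 m; the article does not state that value. The unadjusted standard error is 73.05 × √(2/16) = 25.8 m. Power is from the noncentral t with 28 df unadjusted and 26 df for ANCOVA with baseline and stratum.

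| r | Post-only | Change | ANCOVA | Gain over change |
|---|---|---|---|---|
| 0.5 | 53% | 53% | 65% | 12 points |
| 0.7 | 53% | 75% | 81% | 6 points |
| 0.8 | 53% | 90% | 92% | 3 points |

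The ANCOVA column charges the stratum its degree of freedom but credits it with no variance beyond what baseline explains.

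**4. The same contrast at the planned difference.** At 109.2 m, unadjusted post-only power is 98%.

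**5. Stratum term alone.** The article does not say how much variance GMFCS explains. If it is 10% to 40% (assumed), the error variance is multiplied by 0.90 to 0.60. Power at 54.6 m then rises from 53% to between 57% and 75% (27 df).

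**The case against.** Several stronger readings are tempting, and the document does not support them.

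- **That baseline is ignored.** The effect size is a pre-post difference, and the repeated-measures ANOVA may include Evaluation 1. What is absent is baseline as a covariate.
- **That the ANOVA is run on post-intervention values, with training and tDCS as its two factors.** Those factors are natural for this design, but neither they nor the response is stated. The pre-post effect size points, if anything, towards change scores. The fair baseline comparison therefore includes change scores, where the gain is 12, 6 and 3 points, not the 12, 28 and 39 points seen against post-only values.
- **That the trial has only 53% power.** That figure belongs to an effect halved for illustration. At the planned difference the same contrast has 98%.
- **That the results would be invalid.** Omitting a stratification factor makes tests and intervals conservative. It neither biases the estimate nor inflates the type I error. Stratification also already limits imbalance on GMFCS.

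It can also be said that a condensed article may leave covariates to a fuller analysis plan. That has some force. However, the article does not defer the choice: it names specific tests, and its rank-based alternatives could not hold the terms. Change scores or a time factor would not supply the GMFCS term either, so the stratum part stands on every reading.

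**Conclusion.** The point holds as one of efficiency. The between-group analysis as named omits the stratification factor and uses no baseline covariate, and how baseline enters the two-way ANOVA is left open.

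ANCOVA has the lower variance whichever response was meant. The reduction is 25% to 64% against post-only values and 10% to 25% against change scores, for r from 0.5 to 0.8. The gain from the stratum term cannot be sized from the document. These sizes rest on the assumed correlations, and the power figures also on the assumed 54.6 m effect and the averaged planning SD.

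The stated sample size reproduces without adjustment and does not depend on this change. The change is worth making, but the trial's validity does not hang on it.

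**What to change.** State the primary analysis as an ANCOVA (linear model) of Evaluation 2 Six-Minute Walk distance on:
- tDCS (active or placebo)
- training (treadmill or virtual reality)
- their interaction
- GMFCS stratum (I-II or III)
- Evaluation 1 distance

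Use the same model for the other continuous outcomes, each with its own Evaluation 1 value as the covariate. Naming the response and covariates in advance also settles the ambiguity and prevents their being chosen after the results are seen.

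The cost is two degrees of freedom (28 to 26 in the 32-child case) and a sentence of text. The plan already schedules the data, and the statistical package it names can fit the model.

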## Methods/design

### Primary objective

The primary aim of the proposed project is to perform a comparative analysis of the effects of treadmill training and mobility training with the use of virtual reality with and without tDCS on motor skills and cortex excitability in children with CP between the ages of four and ten years classified on levels I, II and III of the GMFCS.

### Hypothesis 1

The combination of tDCS and either treadmill training or mobility training with virtual reality will achieve greater effects than the isolated use of these training modalities with regard to motor skills and cortex excitability in children with CP between the ages of four and ten years classified on levels I, II and III of the GMFCS.

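### For outcomes judged non-normal, the named tests (Friedman, four-arm Kruskal-Wallis) do not test the active-versus-placebo tDCS contrast of Hypothesis 1

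*Protocol article*

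**What the plan says.** Hypothesis 1 of the protocol article is a between-group claim about the two modalities: "The combination of tDCS and either treadmill training or mobility training with virtual reality will achieve greater effects than the isolated use of these training" (quote cut before its last noun). Under Randomization, "those who meet the eligibility criteria will be randomly allocated to one of the four study groups using a block randomization method". The four groups are treadmill with placebo tDCS (G1), treadmill with active tDCS (G2), virtual reality with placebo (G3) and virtual reality with active (G4). They form a 2×2 layout of modality by stimulation.

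The Statistical analysis section first sets a selector: "The Kolmogorov-Smirnov test will be used to determine whether the data adhere to the Gaussian curve". It then names a parametric and a nonparametric test for each of two questions:

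- "Either repeated-measures ANOVA or Friedman’s test will be used for the statistical analysis of the immediate effects of tDCS";
- "Either two-way ANOVA or the Kruskal-Wallis test will be used for the statistical analysis of the effects of mobility training with and without tDCS".

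The significance rule is general: "All p-values < 0.05 will be considered significant". For non-normal variables the section names no other between-arm comparison: no pairwise follow-up, no comparison of change scores and no rank-based factorial method.

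**The concern.** The two parametric tests can carry a tDCS factor. The two tests named as their replacements cannot, at least in the layout that the pairing implies. An outcome that fails the normality check would therefore not just be analysed with a more robust method; it would be tested against a different null hypothesis. A significant Friedman result could mean only that children improved with training, practice or growth. A significant four-arm Kruskal-Wallis result could mean only that treadmill and virtual reality differ. Because the article attaches both tests to the effect of tDCS, either result could be reported as a tDCS effect.

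The branch is likely to be used. Several outcomes are bounded or item-sum scores: the PEDI categories (sums of 0/1 items), the GMFM-66 (items scored 0–3) and the Berg scale (maximum 56).

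**Working it through.** **1. The plan's own figure.** The Sample size section gives 377.2 ± 93.0 m and 268.0 ± 45.0 m, two-sided alpha 0.05 and 80% power. The difference is 109.2 m. The pooled SD is √((93.0² + 45.0²)/2) = √5337 = 73.05 m, so the standardised difference is 109.2/73.05 = 1.495. Then n = 2 × (1.960 + 0.842)² × 5337/109.2² = 7.03, rounded up to 8 per group. Adding 25% gives 10 per group and 40 in all. The figure reproduces. It matters here only because it fixes the group sizes (8–10) and supplies one documented effect scale.

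**2. What the statistics contain.**

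- Friedman, n children and k = 4 visits: Q = 12/(nk(k+1)) × ΣRⱼ² − 3n(k+1), where Rⱼ is the sum of within-child ranks at visit j. The group label does not appear.
- Kruskal-Wallis, N children in four arms: H = 12/(N(N+1)) × ΣRᵢ²/nᵢ − 3(N+1), on 3 df. With equal arms, H does not change if arm labels are swapped. A pure modality effect (G1 = G2, G3 = G4) and a pure tDCS effect (G1 = G3, G2 = G4) of the same size give H the same distribution.
- Two-way ANOVA, for contrast: the tDCS main effect is (m₂ + m₄ − m₁ − m₃)/2 with standard error SD × √(1/n). The modality effect cancels out.

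**3. Kruskal-Wallis with zero tDCS effect.** Normal outcomes, alpha 0.05, 10,000 simulated trials per row. The modality differences are assumptions, except 1.495 SD, which is borrowed from step 1 as a scale and is not an estimate of treadmill versus virtual reality.

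| Modality difference | Kruskal-Wallis, 8 / 10 per group | ANOVA tDCS main effect, 8 / 10 per group |
|---|---|---|
| 0 | 4.2% / 4.3% | 4.8% / 5.1% |
| 0.5 SD | 15.3% / 19.0% | 5.2% / 5.3% |
| 1 SD | 54.6% / 68.3% | 5.2% / 4.8% |
| 1.495 SD | 90.4% / 96.8% | 4.9% / 4.9% |

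**4. Friedman with zero tDCS effect.** Four visits, the same gain at visits 2–4 in every arm, 4,000 simulated trials. Gain and within-child correlation are assumptions.

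| Shared gain | One arm of 10, correlation 0.5 / 0.8 | 20 active children, correlation 0.5 / 0.8 |
|---|---|---|
| 0 | 4.7% / 4.7% | 4.7% / 4.7% |
| 0.5 SD | 21% / 52% | 47% / 88% |
| 1 SD | 73% / 99% | 98% / 100% |

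A Mann-Whitney comparison of change from baseline between two halves of the 40 children, as for 20 active and 20 placebo, rejected 4.6–5.5% at 10 per group, whatever the shared gain.

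**5. Power for a true 1 SD tDCS effect.** For the main-effect test the noncentrality is 1/√(1/8) = 2.83 on 28 df, giving 78% power at 8 per group, and 1/√(1/10) = 3.16 on 36 df, giving 87% at 10. Simulated Kruskal-Wallis power is 54% and 67%. These match the 1 SD row of step 3 to within simulation error, as the label symmetry in step 2 requires.

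**6. Stability.** Smaller repeat runs gave 16–18% and 54–66% for Kruskal-Wallis in step 3, 21–54% and 75–98% for Friedman in one arm of 10, and 54–67% against 79–87% for power. All lie within about two percentage points of the figures above.

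**The case against.** Five points can be made for the plan.

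*The branch is conditional and may spare the primary outcome.* The Six-Minute Walk Test is a continuous distance planned with means and SDs. In simulation at 10 children, normal data reached the nonparametric branch about 0% of the time with the uncorrected Kolmogorov-Smirnov test and 5% with the Lilliefors correction. For lognormal data (log-SD 0.5) the figures were 0.2% and 19% at 10 children, and 7% and 59% with all 40 pooled. This stands. A reader might infer that Hypothesis 1 as a whole goes untested or that the primary analysis is invalid. The document does not support that, because the parametric branch can carry the contrast.

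*Kruskal-Wallis might mean two arms.* The article generally uses mobility training for the virtual-reality arms. Read literally, the comparison is G3 against G4, where Kruskal-Wallis is equivalent to Mann-Whitney and does test tDCS. It is therefore too strong to say that the test can never do so. But the text does not state the restriction, the pairing with two-way ANOVA points to four arms, and the literal reading leaves the treadmill comparison (G1 against G2) with no named test.

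*Pairwise follow-up is usual and may sit in a fuller plan.* That is fair for Kruskal-Wallis. It does not rescue Friedman's test, whose follow-up compares visits, not groups. The article also does more than omit detail here, since it assigns these tests to these effects.

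*The rejections are not false positives.* Correct. Each test detects a real change over time or a real modality difference. The error arises when the result is attributed to tDCS, as the article's labelling invites.

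*The word immediate.* The article says Friedman or its parametric twin "will be used for the statistical analysis of the immediate effects of tDCS", while the first post-treatment visit is "Evaluation 2: one week following intervention". A reader might infer that the plan claims an effect it cannot measure. The visit schedule is stated openly, and the word plausibly means the short-term visit as opposed to one and three months. This is wording only and adds nothing to the point about test choice.

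**Conclusion.** The point holds for outcomes sent to the nonparametric branch, and the rule is wrong as written for those outcomes. Friedman's test has no active-versus-placebo term under any reading. Kruskal-Wallis fails to isolate tDCS in the four-arm layout that the text implies, and would test it only if confined to an active and a placebo arm of the same modality.

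This structural conclusion needs no assumed numbers. The sizes do: they rest on normal simulated outcomes, modality differences or shared gains of 0.5–1 SD, and within-child correlations of 0.5–0.8, none of which the document gives. On those assumptions, a test labelled as a tDCS test would be significant without any tDCS effect in anything from about one trial in seven to nearly all. Where a 1 SD tDCS effect is real, the omnibus test loses about 20 to 24 percentage points of power (87 − 67 at 10 per group; 78 − 54 at 8).

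**What to change.** In the Statistical analysis section, state that for non-normal outcomes the inferential test is active versus placebo tDCS on change from baseline, stratified by training modality. Suitable choices are a van Elteren test, an aligned-rank factorial analysis, or a permutation test that respects the randomisation strata and blocks. One should be named in advance. Friedman's test can stay as a within-group description of change over visits, with no claim about tDCS attached. If Kruskal-Wallis was meant for two arms only, say so and name the matching treadmill comparison. Replacing the word immediate with a reference to the visit one week after the intervention would remove the side ambiguity.

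The cost is a few sentences and a short script. No new data, visits or children are needed.

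### The Six-Minute Walk Test is named primary, but the aim is wider, every p < 0.05 counts as significant, and no deciding evaluation or contrast is fixed, so the main claim's error rate exceeds the 5% used for sizing

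*Protocol article*

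**What the plan says.** All places are in the protocol article.

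- **Sample size** names one primary outcome, the Six-Minute Walk Test: "This test was selected as the primary outcome based on its proven validity and reliability as a functional capacity assessment tool". The calculation compares "377.2 ± 93.0 m in the experimental group and 268.0 ± 45.0 m in the control group", with "a bidirectional alpha of 0.05 and an 80% test power, eight children will be required for each group". It does not say which of the four arms are the experimental and control groups, or at which evaluation the distance is compared.
- **Primary objective** is wider. It compares the two forms of training "with and without tDCS on motor skills and cortex excitability in children with CP". **Hypothesis 1** uses the same two domains and predicts that tDCS added to either training does better than the training alone.
- **Evaluation and follow-up** lists one evaluation before the intervention and three after it, at one week, one month and three months; the last reads "Evaluation 4: three months following the end of intervention". None is marked as decisive.
- **Statistical analysis** offers repeated-measures ANOVA or Friedman's test for immediate tDCS effects, and two-way ANOVA or Kruskal-Wallis for mobility training with and without tDCS. Neither is tied to the walk test. It then states: "All p-values < 0.05 will be considered significant".

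**The concern.** The named primary outcome and the primary aim do not match. Walking distance cannot measure cortex excitability, so the walk test alone cannot settle Hypothesis 1 as worded. Motor skills could be read from several instruments.

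Even for the walk test, two choices stay open: which of three follow-ups decides, and whether the tDCS question is one pooled comparison or two comparisons, one within each training type. The threshold is stated for every test without distinction.

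The sample size rests on a single test at 5%. If the visit, contrast or outcome that carries the conclusion can be settled once the data are seen, the error rate of the main claim is no longer that 5%. With 10 children per arm, chance differences are large enough for such a choice to matter.

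**Working it through.** **1. The plan's own figure.** Inputs from Sample size: means 377.2 and 268.0 m (difference 109.2), SDs 93.0 and 45.0, two-sided alpha 0.05, power 80%.

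n = (93.0² + 45.0²) × (1.960 + 0.842)² / 109.2² = 7.03, rounded up to 8 per group, as stated. Power at 8 per group is 84.8% by the normal approximation and 79.4% by the t distribution. Adding 25% gives 8 × 1.25 = 10 per group, 40 in all. The figure reproduces, and it is the size for one comparison, one outcome and one time point.

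**2. Walk test alone, with visit and contrast open.** The correlation between visits is not in the document; 0.8 is assumed. For k tests with common correlation ρ and c = 1.96, the chance of at least one two-sided p < 0.05 under no effect is

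1 − ∫ [Φ((c − √ρ·u)/√(1−ρ)) − Φ((−c − √ρ·u)/√(1−ρ))]^k φ(u) du.

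Dropping the second Φ term counts only results in favour of tDCS, for which the nominal level is 2.5%. The two within-training contrasts use different children and are independent.

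| Left open | Two-sided | In favour of tDCS |
|---|---|---|
| Nothing | 5% | 2.5% |
| Two contrasts, one visit: 1 − 0.95² | 10% | 1 − 0.975² = 5% |
| One contrast, three visits | 9.8% | 4.9% |
| Two contrasts, three visits: 1 − (1 − 0.098)² | 19% | 1 − (1 − 0.049)² = 10% |

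Simulation with t tests at 10 children per arm gives the same two-sided values, 10% and 19%, for the three-visit rows. At a visit correlation of 0.5, two contrasts over three visits give 24%; six independent tests would give 1 − 0.95⁶ = 26%.

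**3. Across outcomes, one visit and one contrast.** The document gives no count, so a range is used.

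- *About 11:* the ten assessments listed in the abstract, with motor threshold and motor evoked potential counted separately.
- *21:* walk test 1, Timed Up-and-Go 1, gait kinetics 2, muscles on electromyography 3, motor threshold 1, motor evoked potential 1, PEDI categories 3, GMFM 1, centre-of-pressure axes by eye condition 4, Berg 1, respiratory pressures 2, effort test 1.

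| Outcomes | Two-sided, independent | Two-sided, correlation 0.5 (assumed) | Favouring tDCS, independent | Favouring tDCS, correlation 0.5 |
|---|---|---|---|---|
| 11 | 1 − 0.95¹¹ = 43% | 30% | 1 − 0.975¹¹ = 24% | 15% |
| 21 | 1 − 0.95²¹ = 66% | 43% | 1 − 0.975²¹ = 41% | 22% |

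The favourable share is about half under correlation and up to about three-fifths under independence.

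**4. Effect of fixing the test on sample size**, at the plan's own assumed difference.

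- One named contrast at one visit: 8 per group, unchanged.
- Both within-training contrasts at one visit, Bonferroni alpha 0.025: n = 8.51, so 9 per group; power at 10 per group is 86% (normal) or 81% (t).
- Both contrasts at all three visits, alpha 0.05/6 = 0.0083: n = 10.84, so 11 per group, more than the planned 10.

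**The case against.** The strongest reply has four parts.

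*The threshold is per test.* A reader might infer that a significant result on any outcome would confirm Hypothesis 1, so that a false positive is likely. The document does not say that. It gives a level for each test, names one primary outcome with a reason, and sizes the trial on it. This stands, and the across-outcome figures therefore describe the exposure if the conclusion were drawn from any outcome, not a rule in the plan.

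*The tests are fewer than they could be.* Multiplying 21 outcomes by three visits and two contrasts gives 63 or 126 tests and near-certain error. The plan does not support that count: it names omnibus repeated-measures and two-way ANOVA, not a separate test per visit and per contrast, and one child's visits are not independent. The count of 21 is itself inferred, and includes respiratory pressures and PEDI social function, which are hardly motor skills.

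*Direction matters.* Hypothesis 1 is directional, so only results favouring tDCS could falsely support it. This also stands and roughly halves the figures.

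*Timing and contrast are hinted at, and detail may sit in an analysis plan.* The mention of immediate effects suggests the first follow-up, and a two-way ANOVA could supply a single tDCS main effect. But the two factors are not named, and Kruskal-Wallis, the fallback, provides no such main effect. An unseen analysis plan may hold the multiplicity method, so its absence here is not the point. The mismatch between objective and primary outcome, and the sentence covering all p-values, are stated in this document and need reconciling in it.

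**Conclusion.** The point holds in this limited form. The plan sizes on one outcome, states its aim on two domains, applies one significance threshold to everything, and leaves the deciding visit and contrast of its primary outcome open.

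For the walk test, that means a two-sided error of about 10 to 19% instead of 5%, or about 5 to 10% instead of 2.5% in the favourable direction, given a visit correlation of 0.8. If the conclusion could rest on any of 11 to 21 outcomes, the two-sided chance of at least one nominally significant result is 30 to 43% at correlation 0.5 and 43 to 66% under independence. Both correlations and the outcome count are assumptions. The inflation for the primary outcome is moderate, but it affects the trial's main claim and is easily removed before data are seen.

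**What to change.** - In Statistical analysis, reserve the 0.05 confirmatory test for one named contrast on Six-Minute Walk Test distance at one named evaluation. The tDCS main effect from the planned two-way ANOVA is one suitable choice, with its two factors stated.
- Label all other outcomes, visits and contrasts, including cortex excitability, as secondary. Report them with 95% confidence intervals, and either adjust for multiplicity or do not call them confirmatory.
- Replace the sentence that treats every p-value below 0.05 alike.
- Reword Primary objective and Hypothesis 1 to agree with the primary outcome in Sample size, and say there which arms form the experimental and control groups.

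This is a change of wording and needs no more children. If both within-training contrasts are wanted as confirmatory at one visit, 9 per group suffices by the normal approximation, within the planned 10 provided no arm loses more than one child. The cost is that fewer results can be called significant.
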